## Abstract

**Background::**

The most common and bothersome lower urinary tract complication of diabetes mellitus is diabetic neurogenic bladder (DNB). Acupuncture has certain advantages in treating bladder dysfunction including urinary retention and incontinence. Therefore, we think that electroacupuncture (EA) may be beneficial to DNB patients. However, it is not clear whether EA combined with basic western medicine could optimize the therapeutic effect for DNB.

**Method/design::**

This is a sham-controlled, patient-blinded, pioneer randomized controlled trial (RCT). One hundred fifty eligible patients will be randomly divided into 3 groups: A. basic western medicine (BWC), B. EA with BWC, C. sham EA with BWC. EA treatment will be given twice a week for 12 weeks at bilateral BL23, BL32, BL33, and BL35. The BWC group will received Alpha-lipoic acid (ALA) and methylcobalamin (MC) treatment for 12 weeks, 2 treatment sessions per week. The primary outcome is scored by the 72-hour bladder diary (72h-BD). The secondary outcomes will be scored by the American Urological Association symptom index (AUA-SI), Post-void residual urine volume (PVR) and urodynamic tests. All the assessments will be conducted at baseline and the 12th weeks after the intervention starts. The follow-up assessments will be performed with 72h-BD and AUA-SI in the 4th, 12th, and 24th weeks after intervention ends.

**Discussion::**

This trial protocol provides an example of the clinical application acupuncture treatment in the management of DNB. This RCT will provide us information on the effect of treating DNB patients with only acupuncture, western medicine therapy (ALA + MC) as well as the combination of both. The additive effect or synergistic effect of acupuncture and basic western medicine will then be analyzed.

**Trial registration::**

Chinese Clinical Trial Registry, ChiCTR2000030421.

## Introduction

1

Normal urination requires proper function of both the bladder and the urethra, the process of micturition is controlled by the central nervous system (CNS). Neurogenic bladder includes any lower urinary tract dysfunction caused by the spinal cord injury (SCI) or the CNS lesion or disease.^[1]^ The neurogenic bladder dysfunction (NBD) is a chronic bladder urethra dysfunction, the clinical manifestations of NBD include micturition dysfunction and urine retention. It is reported that the underlying pathological mechanism of NBD is detrusor overactivity and detrusor sphincter dyssynergia.^[2]^ NBD has a high incidence, and about 50,000 patients with NBD are founded every year in China.^[3]^ Many patients with neurologic conditions are complicated by neurogenic bladder dysfunction. It is estimated that the incidence of NBD is 40% to 90% in patients with multiple sclerosis (MS), 70% to 84% in patients with spinal cord injury, 37% to 72% in patients with parkinsonism and 15% in patients with stroke, some patients with diabetic autonomic neuropathy also have NBD.^[4]^ Diabetic neurogenic bladder (DNB) is a manifestation of diabetic neuropathy in the urinary system. Its main features are impaired sensory nerves in the bladder, decreased detrusor contractility, increased bladder capacity, and increased residual urine volume. Related studies found that patients with DNB in clinic often appear urinary system symptoms including urinary incontinence, frequency, and urgency, and have a higher incidence of urinary tract infection and urinary tract obstruction. Meanwhile, patients with DNB are also at risk of serious systemic illnesses including septicemia and acute renal failure if they are not treated properly.^[5]^ According to literature data, the prevalence of DNB in diabetic patients is about 40% to 80%, and even under the condition of good blood glucose control, its incidence is still 25%.^[6]^ Further research shows that the incidence of DNB in patients with diabetes for more than 10 years is as high as 25%, and that of patients with diabetes over 15 years is as high as 50%.^[7]^

Although the increasing incidence of DNB in the Asia-pacific region, but there is no reliable and effective treatment. Therefore, most of the treatment programs of DNB are conservative intervention, nutritional nerve antioxidant to reduce residual urine volume and prevent upper urinary tract injury, while this basic western medicine (BWM) treatment cannot achieve satisfactory effect. The reason for this is that the rehabilitation and reconstruction of bladder function requires long-term intervention, while patients with DNB are usually discharged after acute phase and in early rehabilitation. They usually lack long-lasting interventions, which may lead to a series of complications such as urinary tract infection, urinary injury, and kidney damage. Therefore, longterm, safe and effective treatment has become an urgent need for DNB patients.

Traditional Chinese acupuncture therapy has been successfully used to treat nervous system diseases for thousands of years.^[8]^ In fact, some research on acupuncture for bladder dysfunction has revealed its advantages,^[9–11]^ include relieving symptoms, improving patient quality of life, and delaying the progression of neurogenic bladder dysfunction. Electroacupuncture (EA) has been found to improve chronic urinary retention, decrease urine leakage.^[12,13]^ we believe that EA might be an effective treatment for option for DNB. Besides, it is still unknown whether the combination of acupuncture and BWM therapies could optimize the therapeutic effect. The aim for this randomized controlled trial (RCT) is to clarify the therapeutic effect of acupuncture combined with BWC for DNB.

The purpose of this study is as follows: The first objective of this study is to determine whether EA is effective as compared to a sham EA control on DNB. The second aim for this RCT is to clarify the therapeutic effect of acupuncture combined with BWC for DNB. The findings of this trial will be shared through publication and will provide useful information in forming an optimal acupuncture treatment protocol for DNB.

## Methods/design

2

### Hypotheses

2.1

EA treatment could relieve the urinary system related symptoms and improve the life quality of patients with DNB.

### Objectives

2.2

1.To compare the differences in improvement of urological symptoms, assessed by the American Urological Association symptom index (AUA-SI) and 72-hour bladder diary (72h-BD), between the EA group and Sham EA group.2.To compare the differences in improvement of bladder function, measured by the Urodynamic study and ultrasonic post-void residual urine volume (PVR), between the EA group and Sham EA group.3.To determine the effect of the credibility of acupuncture treatment on the efficacy, as assessed by the credibility of treatment rating scale (CTRS).4.To analyze the additive effect or synergistic effect of EA and BWM treatment for DNB.

### Study design

2.3

We propose a single-center, single-blind, randomized, sham-controlled clinical trial to evaluate the efficacy and safety of EA for neurogenic bladder dysfunction in patients with diabetes mellitus. The trial will be performed at the Hospital of Chengdu University of Traditional Chinese Medicine after ethical approval has been obtained from the Institutional Review Board. A total of 150 eligible patients who meet inclusion criteria will be recruited and randomly divided into the acupuncture group (n = 50), sham acupuncture group (n = 50) and the basic treatment group (n = 50) in a 1:1:1 allocation ratio. After 1 week of washout period, patients will accept 12 weeks of intervention, all treatment will be given twice a week. And the follow-up assessments will be performed in the 4th, 12th, and 24th weeks after intervention ends. The primary outcome will be assessed using the 72h-BD. The secondary outcomes will be measured using the American Urological Association symptom index (AUA-SI) and the PVR, and the urodynamic study. All the assessments will be conducted at baseline, and at the 12th weeks after the intervention starts. The follow-up assessments will be performed with 72h-BD and AUA-SI in the 4th, 12th, and 24th weeks after intervention ends. All participants will sign the informed consent before proceeding with the trial.

The flow chart of the study process is as follows in Figure 1.

**Figure 1 F1:**
[figure not shown]
Flowchart of the trial. Figure shows the flowchart of the study process.

And the timing of treatment assessments and data collection are as follows in Table 1.

**Table 1 T1:**
[figure not shown]
Timing of treatment assessments and data collection.

### Recruitment

2.4

Participants of the study will be recruited through the outpatient clinic or inpatient, hospital-based Wechat advertising, and posters in Hospital of Chengdu University of Traditional Chinese Medicine in Chengdu, Sichuan Province, China. Any patients who are interested will be screened by telephone or on site and consented for the study. After being informed of the details of this research, participants will be asked to signed informed consent, and deliver it to an independent research assistant. Based on the Western medicine treatment, all participants will receive 12 weeks treatment with acupuncture or sham acupuncture and a series of assessments on bladder dysfunction free of charge.

### Inclusion criteria

2.5

Participants meeting all of the following conditions will be included:

1.Aged 18 to 75 years; male or female;2.Participants who meet the diagnostic criteria of diabetes mellitus according to the Standards of medical care for type 2 diabetes in China 2019;^[14]^3.Participants were detection of bladder PVR by trans-abdominal ultrasound, PVR ≥ 100 mL;^[7]^4.Participants with complaints of urinary system symptoms at first visit to the doctor;5.Participants who voluntarily agree with the study and willing to sign the informed consent form for the clinical trial.

### Exclusion criteria

2.6

Participants meeting any one of the following conditions will be excluded:

1.Participants with severe life-threatening primary disease of the cardiovascular, hepatic, renal and hematopoietic system;2.Participants with severe mental disorder;3.Participants had spinal cord injury or other nervous system diseases within the past five years and had undergone pelvic, spinal, and urinary bladder surgery;4.Participants with urinary calculi, infection or tumor within the past 6 months;5.Participants who received acupuncture treatment within the past 6 months;6.Pregnant women.

### Sample size

2.7

The calculation of the sample size in this trial was based on the study about acupuncture treatment for overactive bladder with urge incontinence.^[15]^ Referring to the study, the designer recruited 85 patients and randomly divided into the acupuncture and placebo acupuncture group. And also used frequency of incontinence episodes from the 72h-BD as the main assessment indicator. To detect a clinically meaningful effect of 30% difference between the acupuncture and placebo acupuncture group, 41 cases will be needed in each group. Under the assumption of a significant level of 0.05, 80% power, and 20% dropout rate, a total of 150 participants should be recruited for this RCT (50 participants in each group with 1:1:1 allocation).

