### Primary outcome

4.1

The 72h-BD is a practicable, reliable and effective tool to evaluate the neurogenic bladder related lower urinary tract symptoms.^[18]^ The 72h-BD, which records the frequency of urination, the time of micturition and the urgency of incontinence for 3 days. According to the previous study on this scale to assess bladder-related dysfunction, the frequency of urinary incontinence episodes was selected as the main outcome measurement.^[19]^ The validity of 72h-BD has been validated in patients by the previous clinical studies, and as a non-invasive assessment method, the Chinese version of the scale was verified to be safe and risk-free.^[12]^

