### Statistical analysis

4.6

The intention-to-treat (ITT) analysis will be used in this study. Data analyses will be performed with the use of the statistical software of SPSS version 23.0. The generalized linear mixed model will be used to compare primary and secondary outcomes between groups and test correlation between baseline factors, and the primary and secondary outcomes. All statistical tests will be two-sided, and *P* < .05 is considered statistically significant.

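### The 80% power is stated for an undefined 30% difference and is not supported for the primary outcome, a count of incontinence episodes

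*Protocol article*

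**What the plan says.** The Sample size section (2.7) of the protocol article fixes the size of the main comparison in one sentence: "To detect a clinically meaningful effect of 30% difference between the acupuncture and placebo acupuncture group, 41 cases will be needed in each group". The other inputs are given as "Under the assumption of a significant level of 0.05, 80% power, and 20% dropout rate", which leads to 50 per group and 150 in total. The Statistical analysis section (4.6) adds "All statistical tests will be two-sided".

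The source of the figure is described as follows: "The calculation of the sample size in this trial was based on the study about acupuncture treatment for overactive bladder with urge incontinence". That study, the section says, "also used frequency of incontinence episodes from the 72h-BD as the main assessment indicator". No control mean, standard deviation, dispersion or control proportion is given.

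Section 4.1 makes the endpoint a count: "the frequency of urinary incontinence episodes was selected as the main outcome measurement". No section turns it into a responder proportion. For the analysis, "The generalized linear mixed model will be used to compare primary and secondary outcomes between groups".

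Entry (section 2.5) requires a residual urine volume of at least 100 mL and, on symptoms, only this: "Participants with complaints of urinary system symptoms at first visit to the doctor". Incontinence itself is not required.

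**The concern.** A difference of 30% can mean 30 percentage points between two proportions, a mean count that is 30% lower, or 30 points between two mean percent changes from baseline. These are different targets and need different planning inputs. A reader who tries to recover 41 finds that the two-proportion formula gives it almost without tuning, although the trial has no binary primary endpoint. Every route through the count needs a variability figure, and the article states none.

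The population adds to the doubt. The planning study was in patients with urge incontinence, who have the endpoint by definition. This trial can enrol patients with retention and no leakage, whose count is zero. Zeros raise the variability relative to the mean, and that ratio sets the power for a relative reduction.

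At stake is how a null result would be read. With a stated power of 80%, it would be taken as evidence against a 30% effect, and the article does not show that the design can support that reading.

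**Working it through.** **Inputs.** Two-sided alpha 0.05 (level from section 2.7, sidedness from 4.6), power 80%, 41 evaluable per group, 20% dropout, difference 30%. Control rate, control mean, SD and dispersion are not in the documents; every value used for them below is an assumption.

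**1. Reproducing 41 as two proportions.** The pooled formula is n = [1.960·√(2p̄(1−p̄)) + 0.8416·√(p₁(1−p₁)+p₂(1−p₂))]² / (p₁−p₂)². At 25% v 55%, p̄ = 0.40 and n = [1.960·√0.48 + 0.8416·√0.435]² / 0.09 = (1.358 + 0.555)² / 0.09 = 40.7, giving 41.

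| Control v comparison | n per group |
|---|---|
| 20% v 50% | 38.5 |
| 25% v 55% | 40.7 |
| 30% v 60% | 42.0 |
| 35% v 65% | 42.4 |
| 40% v 70% | 42.0 |
| 45% v 75% | 40.7 |
| 50% v 80% | 38.5 |

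Over this range a one-sided test gives 31 to 34 and a continuity correction 45 to 49, so neither fits.

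**2. Reproducing 41 as two means.** With 41 per group, a two-sample t test has 80% power at a standardised effect of 0.626. A 30% lower mean therefore gives 41 if SD / control mean = 0.30 / 0.626 = 0.48. A 30-point difference in mean percent change gives 41 if its SD is 30 / 0.626 = 48 points. So 41 alone does not reveal the method.

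**3. Power for a 30% lower mean count, 41 per group.** Standardised effect = 0.30 / CV, where CV = SD / control mean, common SD, t test. For baseline adjustment I assume a correlation of 0.6 between baseline and outcome, which multiplies the SD by √(1−0.36) = 0.8.

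| Assumed CV | Unadjusted | Baseline-adjusted |
|---|---|---|
| 0.5 | 77% | 92% |
| 0.6 | 61% | 80% |
| 0.8 | 39% | 55% |
| 1.0 | 27% | 39% |

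**4. The same question as a rate ratio of 0.70.** Negative binomial counts, sham mean m, dispersion k: var(log RR) = [1/m + 1/(0.7m) + 2k] / 41 and power = Φ(0.357/SE − 1.960). For m = 6 and k = 0.5, var = (0.167 + 0.238 + 1.0)/41 = 0.0343, SE = 0.185, and power = Φ(−0.033) = 49%.

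| Dispersion k | m = 3 | m = 6 | m = 9 |
|---|---|---|---|
| 0 (Poisson) | 72% | 95% | 99% |
| 0.25 | 51% | 67% | 74% |
| 0.5 | 40% | 49% | 53% |
| 1.0 | 28% | 31% | 33% |

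**5. What zero counts do.** If a share p of patients has any episodes and all of those have the same number, CV = √(1/p − 1). This is a floor, since real counts also vary among patients who leak. With 20% at zero, CV is 0.50 and unadjusted power at most 77%; with 30% at zero, 0.65 and 54%; with 50% at zero, 1.0 and 27%.

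**6. Dropout.** 41 × 1.2 = 49.2, which gives the stated 50. A 20% loss from 50 leaves 40, one fewer than 41. The difference is trivial, but the restated power should use 40.

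**The case against.** The best defence is that nothing here is shown to be miscalculated. The documents give no variability, and a means calculation with SD about 0.48 of the control mean, or about 48 points of percent change, returns the same 41. The objectives (section 2.2) speak of differences in improvement, so a change-from-baseline reading is natural. The planning study used the same endpoint, and the mean and SD behind 41 may stand in that source or in the full protocol. Low dispersion favours the plan: at a sham mean of 6, unadjusted power is 95% for Poisson counts and 84% at dispersion 0.1. The planned mixed model can handle counts, and its distribution and link are ordinary analysis-plan detail.

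Most of this stands. A reader might infer that the calculation was certainly done for proportions, and that the trial therefore has far less than 80% power for its endpoint. The documents support neither step. The proportion reading is the easiest fit but not the only one, and the low power figures need a dispersion that has to be assumed.

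The defence does not remove the gap in the Sample size section itself. That section states a power and an effect for a named endpoint but leaves the scale of the effect open. Nor does sharing an endpoint with the planning study carry that study's variability over to a population in which incontinence is not an entry requirement.

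**Conclusion.** The concern holds in a limited form. The 30% is undefined, 41 per group matches a 30-point difference between proportions that the trial does not measure, and the 80% power is unsupported for the episode count. It has not been shown to be false.

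If the 30% means a lower mean count, 80% power without adjustment needs a CV of at most about 0.48. Across the assumed values in the tables, unadjusted power runs from 27% to 99%. The lower part of that range is plausible because patients with no episodes can enrol, but that is an inference from the entry criteria, not a figure in the documents. The point should be corrected, since the interpretation of a null result depends on it; it does not invalidate the design.

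**What to change.** Keep the sample size and change two things.

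1. Rewrite the Sample size paragraph on the scale of the primary outcome. Say whether the 30% is a lower mean count (or rate) or a difference in percent change, state the assumed sham mean and variability with their source, and report the power, or the effect detectable with 80% power, at 50 × 0.8 = 40 evaluable per group. At 40 per group the detectable standardised effect is 0.634, so the detectable reduction in the mean count is 0.634 × CV: about 38% at CV 0.6 and 63% at CV 1.0 without adjustment.

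2. Name each patient's baseline 72-hour diary episode count as a covariate in the primary model. The diary is already completed at baseline, so no new data are needed. With an assumed correlation of 0.6, power at 41 per group rises from 61% to about 80% at CV 0.6 and from 27% to about 39% at CV 1.0.

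The count distribution and link can be left to the analysis plan. The cost is one rewritten paragraph and one covariate, with the risk that the stated power or detectable effect becomes less favourable.

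### Sample size: 50 per group with 20% dropout leaves 40 evaluable per group, one fewer than the 41 the protocol says it needs (minor arithmetic inconsistency)

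*Protocol article*

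**What the plan says.** Section 2.7 (Sample size) of the protocol article is the only place where the trial size is justified. The target is stated as "To detect a clinically meaningful effect of 30% difference between the acupuncture and placebo acupuncture group", and for this "41 cases will be needed in each group". The next sentence brings in the significance level, the power and the dropout allowance and draws the conclusion: "Under the assumption of a significant level of 0.05, 80% power, and 20% dropout rate, a total of 150 participants should be recruited", that is, 50 per group under equal allocation.

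Dropout is the only adjustment named between the 41 and the 50. No inflation formula is printed, and the text does not say in so many words that 41 is the number with evaluable outcomes. Section 4.6 (Statistical analysis) adds that "All statistical tests will be two-sided", and that the analysis is by intention to treat with a generalized linear mixed model.

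**The concern.** A dropout allowance should ensure that the required number is still available after the losses. If a fraction *d* of those randomised is lost, the number to randomise is the required number divided by (1 − *d*). Multiplying the required number by (1 + *d*) always gives too few, because the loss applies to the larger, randomised number and not to the completers.

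The figure of 50 looks like the second calculation. If so, group size, dropout rate and power, which the section presents as one set of assumptions, cannot all hold together. At stake is whether the published justification agrees with its own numbers, and by how much the stated power is missed.

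**Working it through.** **Inputs, all from section 2.7 except the sidedness (section 4.6).** Required per group: 41. Dropout: 20%. Recruited: 50 per group, 150 in total. Significance level 0.05, two-sided. Power 80%.

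**Step 1: reproduce the printed figure.** 41 × (1 + 0.20) = 49.2, rounded up to 50 per group; 3 × 50 = 150. This matches exactly.

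**Step 2: check what remains.** 50 × (1 − 0.20) = 40 per group. Since 40 < 41, the requirement is missed by one patient per group. This step does not depend on how the 50 was obtained.

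**Step 3: the size that matches 20% dropout.** 41 / (1 − 0.20) = 51.25, so 52 per group and 156 in total. Rounding only the total gives 3 × 51.25 = 153.75, so 154. The shortfall against 150 is therefore 6 patients (6/150 = 4%) or 4 patients, depending on where one rounds.

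**Step 4: the dropout that 50 per group can absorb.** 1 − 41/50 = 0.18, or 18%.

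**Step 5: power with 40 per group, taking 41 at face value.**
- Suppose 41 per group gives exactly 80%. By the normal approximation the implied standardised difference is (1.960 + 0.842) × √(2/41) = 0.619. With 40 per group, power is Φ(0.619 × √(40/2) − 1.960) = 79.0%. The two-sample t-test gives the same answer (standardised difference 0.626, power 79.0%).
- That is the lower end. A sample size is normally rounded up, so the unrounded requirement would lie somewhere above 40 and up to 41. If it were only just above 40 (standardised difference close to 0.626 by the normal approximation), power with 40 per group would be just under 80%.
- The range is therefore about 79.0% to just under 80%.

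**Step 6: can the 41 be checked?** Not from the article. It does not say whether the 30% is relative or absolute, or whether it concerns means or proportions, and it gives no standard deviation or control value. If one *assumes* a 30-percentage-point difference between two proportions, the requirement runs from 22 to 43 per group depending on the control rate, and equals 41 at 25% versus 55% or at 45% versus 75%. In those two cases power is 80.3% with 41 per group and 79.3% with 40, again a loss of about one point.

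**The case against.** The strongest reply is that this makes no practical difference, and most of it stands. The gap is one completer per group and at most about one percentage point of power. That is much smaller than the uncertainty about the 41 itself. The difference between 150 and 156 also owes something to rounding up in each group; before rounding, it is 51.25 against 50.

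It can also be said that the method is a reconstruction. That is right: 41 × 1.2 fits, but choosing a convenient round number would also give 50. The article does not prove that 20% was added on. The mismatch between 40 and 41 does not need that inference, however. It needs only that 41 is the number before dropout. If 41 already contained the allowance, nothing in the section would explain the step to 50, since 3 × 41 = 123.

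A third reply is that the mixed model uses partial data. This is partly right. The bladder diary is scheduled at baseline, at week 12, and at 4, 12 and 24 weeks after treatment ends, so a patient lost after week 12 still contributes the end-of-treatment value. Sections 2.3 and 4.1 describe no diary assessment between baseline and week 12, so a patient lost during treatment adds almost nothing to the comparison of the groups. Counting the whole 20% as lost is therefore pessimistic, but it is the discount that the sample-size section itself applies.

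A reader might infer that the trial is underpowered, or that its sample-size justification collapses. The documents do not support that. The loss is about one point at worst, and it is conditional on a 41 that cannot be verified in either direction.

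**Conclusion.** The inconsistency is real and minor. On the section's own figures, 50 per group with 20% dropout leaves 40 evaluable, not 41, and nothing elsewhere in the article repairs this. The matching size would be 52 per group.

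The conclusion rests on reading 41 as the number needed before dropout, which the order of the text supports. The power figure also takes 41 at face value and counts every dropout as contributing nothing. The design, the planned analysis and the interpretation of the result are not affected.

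**What to change.** Keep 150 and restate one sentence in section 2.7, in one of two ways:
- 50 per group allows for 18% dropout, leaving 41 evaluable per group; or
- with 20% dropout, 40 evaluable per group remain, and power is about 79%.

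Either version makes the numbers agree. The cost is one sentence and a slightly less favourable stated figure. If the sponsor prefers to keep both 20% dropout and 80% power as written, the size that goes with them is 52 per group, 156 in total, at the cost of six more patients. The shortfall is too small to require that.
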